Clinical deterioration will refer to worsening of anxiety, depressive symptoms, emotional instability, or psychosocial functioning identified through clinical evaluation, psychotherapy sessions, or validated clinical scales during follow-up. If deterioration is suspected, participants may undergo additional diagnostic evaluation using the Structured Clinical Interview for DSM-5-TR (SCID-5-TR) and other clinically relevant assessments.

Clinical Management:

Should symptoms arise requiring pharmacological treatment or additional psychiatric support, psychiatric consultation will be available within the Mental Health Unit of the same institution. Each case will be individually evaluated, and appropriate clinical measures may include extension of psychotherapy, referral to long-term psychotherapy, psychiatric treatment, or other clinically indicated interventions.

Withdrawal Criteria:

Participants may be withdrawn from the study in cases of severe clinical deterioration, serious adverse events, emergence of psychiatric conditions requiring immediate alternative treatment, participant request, non-adherence to study procedures, or investigator judgment that continuation may compromise participant safety or study integrity.

Protocol Deviations:

All protocol deviations, including missed sessions, incomplete assessments, deviations from intervention procedures, or unplanned clinical management modifications, will be documented and reviewed by the investigators. Any clinically relevant deviation affecting participant safety or trial conduct will be reported to the ethics committee when required.

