### 2.8. Roles and Confidentiality

The study will be conducted at the Onofre Lopes University Hospital (EBSERH), Federal University of Rio Grande do Norte, using institutional clinical infrastructure without additional costs to participants. As there is no external commercial or financial sponsor, no external party is involved in study design, data collection, analysis, interpretation of data, manuscript preparation, or publication decisions. The investigators retain full scientific independence.

Allocation confidentiality will be managed by a designated investigator with restricted access to the randomization key, which will be securely stored in a password-protected file. This role is strictly administrative and limited to data governance.

Clinical interviews for eligibility confirmation will be conducted by trained clinical personnel according to DSM-5-TR criteria prior to inclusion.

Biological samples will be processed and stored by a dedicated researcher responsible for the biorepository, using coded identifiers stratified by sex to ensure confidentiality and traceability.

Statistical analysis will be performed by an independent data analyst using de-identified datasets, ensuring separation from clinical and intervention procedures.

Participant data will be coded at enrollment using official documentation. All datasets will be stored in encrypted, password-protected systems managed by the responsible researchers, with identification keys retained by the principal investigator to ensure confidentiality and traceability.

In cases of dropout or exclusion, participants will be retained in the intention-to-treat analysis, with identification keys remaining under the custody of the principal investigator, and all procedures will be duly documented, including reasons for exclusion, with missing data handled using appropriate statistical methods.

Strategies to ensure treatment adherence include institutional communication, structured scheduling, and clear guidance provided at informed consent, with emphasis on confidentiality and protocol compliance.

No Data Monitoring Committee will be established, and no interim analyses are planned due to the low-risk outpatient nature of the study. The study will be supervised by the investigators with clearly defined roles across trial activities. The principal investigator will oversee protocol compliance without involvement in intervention delivery or data analysis.

Therapist Training and Fidelity:

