### 2.11. Statistical Methods

The primary analysis (Phase 1) will compare BATF versus Brief Focal Psychotherapy in a combined sample of participants with anxiety and/or depressive symptoms, irrespective of diagnostic category (“collapsed” clinical conditions). This analysis represents the primary confirmatory comparison of the trial.

Exploratory subgroup analyses within Phase 1 are pre-specified and will evaluate treatment effects separately in participants with anxiety and depressive symptoms.

The secondary analysis (Phase 2) will examine a pre-specified 2 × 2 factorial analytical framework (intervention × clinical condition), allowing assessment of main and interaction effects across four groups (BATF-depression, BATF-anxiety, control-depression, and control-anxiety), resulting in four analytical cells for the 2 × 2 factorial analysis.

For Phase 1, the primary comparison between BATF and Brief Focal Psychotherapy will be performed using Student’s *t*-test for normally distributed change scores or the Mann–Whitney U test when normality assumptions are not met. The first phase will include 156 participants.

Phase 2 will include a total sample of 472 participants (including participants from Phase 1 plus additional recruited participants). Change scores will be compared across the four predefined groups (BATF-depression, BATF-anxiety, control-depression, and control-anxiety) using one-way analysis of variance (ANOVA) or the Kruskal–Wallis test, as appropriate.

Assessments performed at Week 4 will be used to describe intermediate clinical evolution and may support exploratory analyses of treatment trajectories.

Effect Size Measure: Omega squared (ω^2^); Statistical Significance Level: α = 0.05.

Multiplicity for the co-primary outcomes will be controlled using the Holm–Bonferroni procedure. Secondary and subgroup analyses will be considered exploratory and interpreted accordingly. Exploratory biomarker analyses will apply false discovery rate (FDR) correction according to the Benjamini–Hochberg method.

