Primary Analysis: Recruitment will be continuous, and allocation will follow a pre-generated 1:1 randomization sequence, stratified by clinical condition. Participants will be enrolled until the target sample size of randomized participants is reached. All analyses will follow the intention-to-treat principle. Missing outcome data will be handled primarily using maximum likelihood estimation within mixed-effects models. Multiple imputation may be performed as a sensitivity analysis, when appropriate, to evaluate the robustness of the findings.

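### Withdrawal from the study for deterioration or non-adherence, with no stated follow-up afterwards, can lose outcome-related Week-13 scores and undermines the intention-to-treat analysis

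*Protocol article*

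**What the plan says.** Section 2.4 (Withdrawal Criteria) reads "Participants may be withdrawn from the study in cases of severe clinical deterioration, serious adverse events". The list goes on to psychiatric conditions that need other treatment at once, and ends with "participant request, non-adherence to study procedures, or investigator judgment that continuation may compromise participant safety or study integrity". The same section defines clinical deterioration as worsening that includes anxiety and depressive symptoms, found at clinical evaluation, in therapy sessions or on the scales.

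Section 2.8 says "In cases of dropout or exclusion, participants will be retained in the intention-to-treat analysis", and adds that missing data will be handled by suitable statistical methods.

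Section 2.11 says "All analyses will follow the intention-to-treat principle" and "Missing outcome data will be handled primarily using maximum likelihood estimation within mixed-effects models", with multiple imputation as a possible sensitivity analysis. The same section says that the Phase 1 primary comparison "will be performed using Student’s *t*-test for normally distributed change scores or the Mann–Whitney U test". Under Additional Analyses, the repeated-measures mixed model is an optional sensitivity analysis.

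The primary endpoint is change from baseline to Week 13, with scales at Weeks 0, 4 and 13 (section 2.5). No section says whether the Week-13 scale is sought from someone who has been withdrawn.

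**The concern.** Intention-to-treat needs two things: every randomised participant in the analysis set, and outcomes collected whatever treatment was received. The article promises the first. On the second it states a rule that ends study participation on grounds close to the primary outcome itself, since worsening of the symptoms that MADRS and HAM-A measure is one of them. Section 2.8 then treats the data of people who leave as missing.

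If the rule is applied as written, an arm can lose some of its worst Week-13 values, and its remaining mean looks better than it should. If this happens more in one arm, or to different kinds of participant, the between-arm difference shifts. The comparator meets weekly for up to ten sessions. BATF meets on day 1, at Week 4 and optionally at Week 13, so it has no planned session between Weeks 4 and 13. The comparator therefore offers more occasions to notice deterioration or missed procedures. Therapists know the allocation (section 4).

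**Working it through.** **The plan's own figure.** Inputs from section 2.10: difference 5, SD 11, two-sided alpha 0.05, power 80%, 1:1 allocation.
- Normal approximation: n = 2 × (1.960 + 0.842)² × (11/5)² ≈ 76 per group.
- Exact noncentral t with d = 5/11: 76.95, so 77 per group. The stated figure reproduces. Power is 80.0% at 77 and 80.5% at 78 per group.

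**How the sections fit together.**
- Section 2.4 ends study participation, section 2.8 keeps the person in the analysis set, and section 2.11 needs a Week-13 change score for the t-test or Mann–Whitney test. The three meet only if the score is collected or a model supplies it.
- The model that could supply it (maximum likelihood in a mixed model) is named for missing data but is not the primary test, and appears elsewhere only as an optional sensitivity analysis.
- Maximum likelihood is unbiased if recorded scores explain the withdrawal (missing at random). Deterioration that arises between Weeks 4 and 13 and leads to withdrawal has no scheduled score, so the assumption is doubtful there.

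**Size in one arm, completers only.** If the worst share q of an arm's Week-13 changes is unobserved and changes are normal with SD 11, the completer mean looks better by 11 × φ(z)/(1 − q), where z is the 1 − q normal quantile.
- q = 2%: 0.54 points
- q = 5%: 11 × 0.1031/0.95 = 1.19
- q = 10%: 11 × 0.1755/0.90 = 2.14
- q = 15%: 3.02

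**Size in the contrast, completers only.** With 10% lost in one arm and 5% in the other: 2.14 − 1.19 = 0.95 points, and 0.95/5 = 19% of the target difference. With equal losses of the same kind it is about 0.

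**What maximum likelihood changes.** This was simulated with SD 11, an assumed correlation of 0.5 or 0.7 between Week-4 and Week-13 change, and Week 4 recorded for everyone. Figures are single-arm bias in points, for correlation 0.5 / 0.7.

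| Withdrawal driven by | Share lost | Completers | Maximum likelihood |
|---|---|---|---|
| unseen Week-13 value | 5% | 1.18 / 1.19 | 0.92 / 0.66 |
| unseen Week-13 value | 10% | 2.14 / 2.15 | 1.73 / 1.28 |
| recorded Week-4 value | 5% | 0.58 / 0.83 | about 0 |
| recorded Week-4 value | 10% | 1.07 / 1.50 | about 0 |

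For 10% against 5% lost, the contrast bias is as follows.
- Unseen Week-13 value, maximum likelihood: 1.73 − 0.92 = 0.81, or 1.28 − 0.66 = 0.62.
- Recorded Week-4 value, completers: 1.07 − 0.58 = 0.49, or 1.50 − 0.83 = 0.67. Maximum likelihood gives about 0.

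So even when recorded scores explain the withdrawal, the named test applied to completers keeps a bias that the optional model would remove.

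The documents give neither the withdrawal shares nor the correlation. SD 11 is the MADRS planning value; no SD is given for HAM-A.

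**The case against.** A reader might infer that the rule removes the worst outcomes, that Week-13 scores of withdrawn participants will never be collected, and that no model in the plan can repair this. The article does not support that.
- Withdrawal is permissive and the deterioration must be severe. Section 2.4 also allows worsening to be managed case by case, including by extending therapy or by psychiatric treatment.
- Medication changes during the study are to be documented and considered in sensitivity analyses (section 2.3.2), and missed sessions are logged as deviations. The optional per-protocol analysis and the adjustment for sessions attended presuppose that some incomplete attenders remain in the data.
- Maximum likelihood is named as the main approach to missing data. It removes the bias when withdrawal follows recorded scores and reduces it otherwise.
- Equal losses with the same relation to outcome leave the contrast nearly unbiased. The session counts are maxima, and nothing in the article shows unequal losses.

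These arguments limit the strength of the point and all of them stand. It can also be said that follow-up after stopping therapy is a detail for the full protocol or the SAP. That carries less weight, because the article states a rule ending participation on outcome-related grounds alongside its intention-to-treat promise, and names a primary test that cannot use those participants.

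**Conclusion.** The point holds in a limited form. The withdrawal rule, with no stated outcome collection afterwards, undermines the intention-to-treat analysis without necessarily defeating it. It leaves the result resting on a missing-at-random assumption that is doubtful for deterioration between Weeks 4 and 13, and on a mixed model that is not tied to the primary test.

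Bias in the treatment contrast is possible and, given the session schedules, plausible, but it is not demonstrated. At assumed losses of 10% and 5% of the worst outcomes it is about 0.95 points for completers and 0.62 to 0.81 under maximum likelihood, against a 5-point target. It is about 0 if losses are alike in both arms, or if recorded scores explain the withdrawal and maximum likelihood is used. These figures show scale and are not forecasts.

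Loss of power is a separate matter that the authors already disclose (sections 2.10.2 and 4). For reference, 10% loss leaves 70 per arm and 76.1% power.

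**What to change.** Reconcile the Withdrawal Criteria in section 2.4 with sections 2.8 and 2.11, before recruitment starts (anticipated in the fourth quarter of 2026), because uncollected scores cannot be obtained later.
- Separate stopping study therapy from ending outcome follow-up. Leave the clinical criteria and the investigators' safety discretion unchanged.
- State that participants who stop therapy for any reason, including non-adherence, are still asked to complete the scheduled Week-4 and Week-13 scales, unless they withdraw consent for follow-up or the investigator judges further contact unsafe.
- Analyse every collected value in the randomised arm, whatever therapy was received.
- Say how the primary comparison uses participants who still lack a Week-13 value, so that the t-test or Mann–Whitney test and the maximum likelihood statement agree.

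The cost is a short amendment and some effort to reach people who stopped therapy. It needs no new visits or instruments.

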### 2.5. Outcomes

The objective of this study is to evaluate the effects of a brief psychotherapeutic intervention, BATF, compared with Brief Focal Psychotherapy in reducing symptoms of anxiety and depression.

Outcomes include quantitative measures of depressive and anxiety symptoms, sleep quality, and exploratory salivary and blood biomarkers associated with stress, inflammatory processes, and neurobiological function.

The co-primary outcomes for Phase 1 are defined as the change from baseline (Week 0) to Week 13 in symptom severity within each diagnostic stratum, assessed using disorder-specific scales (MADRS for depressive disorder and HAM-A for anxiety disorder).

Clinical diagnoses will be established during baseline psychiatric and clinical evaluation according to DSM-5-TR criteria prior to randomization. Participants will be stratified according to their primary clinical condition (anxiety or depressive disorder) and randomized to one of the two psychotherapeutic interventions. Each participant will be assessed only with the symptom severity scale corresponding to their primary diagnosis.

Secondary outcomes include depressive and anxiety symptom severity assessed using disorder-specific instruments according to participants’ primary clinical condition (PHQ-9 for depressive disorders and GAD-7 for anxiety disorders). Sleep quality, assessed using the Pittsburgh Sleep Quality Index (PSQI), and exploratory biomarker analyses will be performed in all participants.

Exploratory outcomes include salivary and blood biomarkers. Salivary biomarkers include cortisol, glutamate, immunoglobulin A (IgA), lysozyme, melatonin, alpha-amylase, chromogranin A, and fibroblast growth factor 2 (FGF2). Blood biomarkers include cortisol, pro–brain-derived neurotrophic factor (pro-BDNF), mature BDNF, sex hormones, dehydroepiandrosterone (DHEA), C-reactive protein (CRP), growth hormone, and glutamate. Cortisol and glutamate will be assessed in both saliva and blood samples. All biomarkers are pre-specified in the Statistical Analysis Plan and will be considered exploratory and hypothesis-generating.

Assessments will be conducted at baseline (Week 0), Week 4, and Week 13. The primary endpoint is defined as change from baseline (Week 0) to Week 13, and all outcomes will be analyzed according to the pre-specified statistical analysis plan using change-from-baseline metrics. Continuous outcomes will be summarized using group means and standard deviations or medians and interquartile ranges, depending on data distribution.

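### Change from baseline is fixed for every outcome, including 16 exploratory biomarker entries, with no adjustment for baseline marker level; for skewed concentrations this loses precision

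*Protocol article*

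**What the plan says.** Section 2.5 (Outcomes) of the protocol article sets one rule for the whole trial: "all outcomes will be analyzed according to the pre-specified statistical analysis plan using change-from-baseline metrics". The same section lists the laboratory outcomes:

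- **Saliva, eight entries:** "Salivary biomarkers include cortisol, glutamate, immunoglobulin A (IgA), lysozyme, melatonin, alpha-amylase, chromogranin A, and fibroblast growth factor 2 (FGF2").
- **Blood, eight entries:** cortisol, pro-BDNF, "mature BDNF, sex hormones, dehydroepiandrosterone (DHEA), C-reactive protein (CRP), growth hormone, and glutamate". Sex hormones form one entry for an unstated number of analytes.

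On their status, Section 2.5 states: "All biomarkers are pre-specified in the Statistical Analysis Plan and will be considered exploratory and hypothesis-generating". It adds that "exploratory biomarker analyses will be performed in all participants".

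Section 2.11 (Statistical Methods) names tests for change scores. For the Phase 1 primary comparison they are a t-test or Mann-Whitney test, and for the four groups of Phase 2 a one-way ANOVA or Kruskal-Wallis test. None has a baseline term. The only sentence there specific to biomarkers is on multiplicity: "Exploratory biomarker analyses will apply false discovery rate (FDR) correction".

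The subsection on additional analyses allows adjusted models as optional sensitivity analyses. They name baseline symptom severity, concomitant medication and adherence, but not baseline marker level or sex. Section 2.8 mentions sex only for sample coding ("using coded identifiers stratified by sex to ensure confidentiality and traceability"). Section 2.9.1 records menstrual phase and contraceptive use for possible sensitivity analyses.

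**The concern.** Assay concentrations such as CRP, cortisol, DHEA, growth hormone and IgA are positive and usually right-skewed, and the size of an absolute change tends to grow with the starting level. Two separate inefficiencies follow from a change-score rule.

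1. On any scale, an unadjusted change score subtracts the whole baseline value, although the follow-up value is only partly correlated with it. Using baseline as a covariate removes that excess noise.
2. If the change is taken on the raw scale, the few participants with high baselines supply most of the variance. For a marker whose level differs greatly between the sexes, the sex with the higher level supplies most of it.

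Exploring biomarkers is a stated aim of the trial. It costs each participant 30 mL of fasting blood and three home saliva samples at each sampling occasion, and the results face a Benjamini-Hochberg correction over many tests. What is at stake is the chance of detecting a real proportional effect on a marker.

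**Working it through.** **The plan's own figure.** The article gives a sample size only for MADRS: difference 5, SD 11, two-sided 5% level, 80% power. The exact noncentral-t solution is 76.95 per group, so 77, with power 0.800 at 77 and 0.805 at the adopted 78. The stated figure reproduces. No biomarker power is stated, so none can be contradicted.

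**Step 1: loss from not adjusting, on any one scale.** Take SD σ at both visits and correlation ρ. With n per arm, the variance of the arm contrast is:

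- change score: 2σ²(1−ρ) × 2/n
- ANCOVA: σ²(1−ρ²) × 2/n
- ratio, ANCOVA to change: (1−ρ²) / [2(1−ρ)] = (1+ρ)/2

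The ratio is 0.65, 0.75, 0.80 and 0.85 at ρ = 0.3, 0.5, 0.6 and 0.7. At ρ = 0.6, ANCOVA needs 80% of the sample that a change score needs.

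**Step 2: a hand check on the log scale.** Assume log-SD 1.0, ρ = 0.6, a 30% reduction (log 0.7 = −0.357) and n = 78, so √(2/78) = 0.160.

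- Log change: SE = √0.8 × 0.160 = 0.143; z = 2.49; power = Φ(2.49 − 1.96) = 70%.
- Log ANCOVA: SE = 0.8 × 0.160 = 0.128; z = 2.78; power = Φ(2.78 − 1.96) = 80%.

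**Step 3: simulation with the raw scale included.** Log-normal marker, ρ = 0.6, 78 per arm, level 0.05, no FDR penalty. None of these marker inputs is in the article. In scenario C the marker is 15 times higher in one sex (30% of the sample), and the ANCOVA includes sex.

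| Scenario | Raw change, t-test | Raw change, Mann-Whitney | Log change, t-test | Log ANCOVA |
|---|---|---|---|---|
| A: log-SD 1.0, 30% fall | 36% | 53% | 70% | 79% |
| B: log-SD 0.8, 30% fall | 60% | 75% | 87% | 93% |
| C: log-SD 0.35, 15% fall, 15-fold sex ratio | 44% | 78% | 90% | 95% |

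A repeat with 3,000 trials per scenario agreed to within about 2 percentage points.

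**Step 4: the Phase 2 sample.** With the same effects and 472/2 = 236 per arm, compared as two arms, Mann-Whitney on raw change gives 95%, 99.6% and 99.7%. Log change and log ANCOVA both exceed 99%. The raw-change t-test gives 76%, 96% and 89%. The gap closes because power nears its ceiling. If the effect is instead made small enough that log ANCOVA (plus sex) has about 80% power at 236 per arm (log-SD 0.5 or 1.0, ρ 0.5 or 0.7, sex ratio 1 or 10), log change has 68 to 74%, Mann-Whitney 52 to 68% and the raw t-test 20 to 63%.

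**Step 5: who drives a raw change score.** Across the settings of Step 4, at 78 and 236 per arm and with 70% women:

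- no sex difference: the top baseline quartile carries 53 to 79% of the sum of squares, and men (30% of the sample) carry 29 to 30%;
- 10-fold sex difference: the top quartile carries 89 to 96%, and men carry 96 to 97%.

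**Step 6: is there bias?** With a 15-fold sex difference and no treatment effect, rejection rates were 4.4% (t-test) and 5.0% (Mann-Whitney), close to nominal.

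**The case against.** The strongest reply is that the SAP exists and is not shown, and that the rule in Section 2.5 itself refers to it. Log or percent change is also a change-from-baseline metric. Transformation, covariates, sex-specific models and detection limits for exploratory assays are what a condensed article leaves to its SAP. The t-test and Mann-Whitney test are assigned to the Phase 1 primary comparison, not to biomarkers. If that rule were extended to them, strongly skewed data would go to the rank test, so the lowest power figures would not arise. The biomarkers are exploratory, and no power is claimed for them.

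Much of this stands. A reader might infer that concentrations will be analysed untransformed and pooled over the sexes, and that one sex will dominate the results. The article says neither of the first two. The third would hold only on the raw scale, for sex hormones and markers with a similarly large sex difference. Nor do the documents support the idea that the arm contrast would systematically reflect the sex mix: arms are randomised, each person's own level is subtracted, and the null rejection rate stays near 5%.

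What does not stand is that nothing is fixed. The article says what the SAP does, namely use change from baseline for all outcomes, and even log change, the most favourable reading, is less efficient than a baseline-adjusted model. The optional repeated-measures sensitivity model does not clearly repair this. With baseline as one of the responses, complete data and no constraint that arms share a baseline mean, its arm-by-time contrast is again the change-score difference.

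**Conclusion.** The point holds as one of efficiency, at minor severity. The stated rule commits 16 biomarker entries to change from baseline, and no stated analysis uses the baseline marker level as a covariate. On the most favourable reading (log change), the cost at 78 per arm is 5 to 9 percentage points of power in the scenarios tried. Losses of 17 to 26 points (Mann-Whitney) or 33 to 51 points (t-test) against log ANCOVA arise only if raw change is analysed, which the article does not say. For the same effects at 236 per arm the loss is small except with a raw-change t-test, though smaller effects would again show it.

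These sizes rest on assumed log-SDs, visit correlation, effects and sex ratio, and they ignore the FDR correction. The consequence is lost precision, not bias. The clinical scales and the confirmatory comparison are not touched by it.

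**What to change.** In Sections 2.5 and 2.11, limit the change-score rule to the clinical scales. For each concentration, specify:

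- a linear model of the log follow-up value on arm, log baseline value and clinical condition;
- sex as a further term for sex-dependent markers, with sex hormones analysed by sex or with a sex-specific baseline slope;
- the adjusted ratio of geometric means with its 95% CI as the reported effect, and its p-value as the input to the Benjamini-Hochberg step.

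If the SAP already does this, only the sentence in Section 2.5 needs correcting so that the two agree.

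The cost is wording. Baseline samples are already planned and sex is already coded on them. Recruitment is not due to begin until the fourth quarter of 2026, so the change can be made before any outcome is seen. The downsides are that results become ratios rather than absolute units, and that values below the detection limit need a stated rule.
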